#### HELM mediators

Educators will complete the School Implementation Leadership Scale (S-ILS) [55], a 21-item measure that assesses seven subscales of implementation leadership: knowledgeable (understanding of RUBIES and implementation issues), supportive (support for RUBIES use), proactive (anticipating and addressing challenges), perseverant (consistent and responsive to challenges), communicative (shares implementation related information with staff), has a vision/mission (oriented towards using RUBIES), and available in implementing RUBIES [5, 37]. The S-ILS is a psychometrically validated and reliable instrument (α = 0.95–0.98). Implementation leadership scores are generated for a school at each timepoint (implementation baseline, Weeks 16, 24, 52, and 76) by aggregating individual educator ratings to the school level.

Educators also will complete the School Implementation Climate Scale (S-ICS) [56], a 21-item measure that assesses seven subscales of implementation climate: focus, educational support, recognition, rewards, use of data, existing supports, and RUBIES integration [37, 56]. The S-ICS is a psychometrically validated and reliable instrument (α = 0.81–0.91; 39, 79). Implementation climate is scored by aggregating individual educator ratings to the school level.

#### Qualitative interviews

We will use a sequential (QUAN QUAL) mixed-methods design to understand discrepancies in implementation behavior (e.g., schools with high implementation leadership and low RUBIES fidelity and sustainment [57]. The functions are *sampling* (using quantitative data to identify the qualitative sample) and *expansion* (using qualitative data to provide depth and breadth of understanding of factors that contribute to outcomes that deviate from the theory of change), and the process is *connecting *(qualitative data will build on quantitative data) [57–59].

Interview questions will explore the implementation determinants and mechanisms [41, 60, 61]. Individual semi-structured interviews (approximately 30–45 min) will be conducted via Zoom at a convenient time for educators. The interview guide will be developed using the Exploration, Preparation, Implementation, and Sustainment framework [62] to examine multilevel determinants that explain what processes facilitated or hindered educators’ RUBIES sustainment. Interviews will be audio-recorded, then transcribed prior to coding. Interviews will be continuously conducted until we achieve thematic saturation.

### Data analysis

Preliminary data checks and analyses will screen for errors and explore normality, linearity, form, and outliers as well as psychometric characteristics of all latent constructs. Comparisons of intervention effects will use an intent-to-treat approach.

### Aim 1 analyses

Aim 1 evaluates the main effect of RUBIES vs. educator psychoeducation on child externalizing behavior among children in Year 1 of study enrollment. The primary outcome for this comparison is change in child externalizing behavior from baseline to Week 24, contrasting all groups assigned to RUBIES vs. educator psychoeducation (i.e., arms 1 & 2 vs. arm 3). We will fit a three-level Linear Mixed Model (LMM) as follows: the Level 1 model (piece wise time) with a “knot” (i.e., inflection point) at Week 16 used to capture each child’s change in externalizing behavior from Baseline to Week 16, and potentially different slope from Week 16 to Week 24. At Level 2 (child/educator; due to 1:1 pairing), each growth parameter will be modeled as a function of an intercept and child/educator-level covariates. We will select covariates by testing for differences across arms on youth and educator characteristics; covariates will be included if the effect size ≥|0.2|. At Level 3 (school), we will include a random intercept to account for the nesting of the child-educator dyads within schools and a treatment assignment indicator ([RUBIES + HELM] + [RUBIES only] vs. educator psychoeducation). We will test the interaction effect of treatment condition with time. Linear combinations of the growth parameters from this model will be used to test whether improvement in child externalizing behavior was superior for autistic children assigned to [RUBIES + HELM] + [RUBIES only] vs. educator psychoeducation from Baseline to Week 24.

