### Randomization

The biostatistician (WS) will generate the random allocation sequence; all other research team members will not have access to the randomization sequence. Schools in each cohort will be randomized (1:1:1) to one of three parallel arms (*n* = 14 schools per arm): 1) RUBIES + HELM; 2) RUBIES only; 3) or educator psychoeducation. Randomization will be stratified based on median split for: 1) size of school at the time of enrollment; and 2) number of possible dyads (identified at screening for each enrollment cohort). Study enrollment, randomization, and engagement for all schools begins in the Spring prior to Year 1. Schools randomized to psychoeducation will be enrolled in the trial for one year; schools randomized to either RUBIES + HELM or RUBIES only will be enrolled in the trial for two years; children will be enrolled for one year.

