The IE also will rate the Clinical Global Impressions-Sustainment scale (CGI-S, secondary implementation outcome), an adapted version of the Clinical Global Impressions-Improvement scale. The CGI-S will be rated by the IE on a 7-point scale from 1 “very much improved”, to 4 “no change” to 7 “very much worse.” To inform CGI-S ratings, a standardized questionnaire followed by IE interview will be conducted with educators at implementation baseline to establish a benchmark of the educator’s baseline skills. The questionnaire allows the educator to endorse whether, at baseline, they use any of 26 specific RUBIES strategies (yes/no response). The interview between IE and educator then focuses on characterizing the quality and frequency of endorsed strategies. Finally, the IE will use all information to characterize the educator’s overall skill mastery at baseline on a 7-point scale (1 “exceptional mastery”; 4 “developing mastery”; 7 “no demonstrated mastery”), which will allow the IE to standardize subsequent CGI-S ratings across educators who have variable foundations in behavioral strategies at baseline. At Weeks 16, 24, 52, and 76, the educator will update their current strategy “use” ratings and then meet with the IE to update characterization (quality/frequency) of the utilized RUBIES strategies. Using this updated information, the IE will complete the CGI-Sustainment rating (i.e., is the current use of educator RUBIES strategies 1 “very much improved”, 2 “much improved”, 3 “minimally improved”, 4 “no change”, etc. from baseline). RUBIES sustainment at Weeks 52 and 76 will be calculated as a binary variable: strategies “sustained” over time (Score of 1 or 2 – Much improved to very much improved from baseline) vs strategies not “sustained” over time (Score of ≥ 3: No Change to Very Much Worse from baseline).

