### Aim 2 analyses

Aim 2 compares the effect of HELM vs. educator coaching on RUBIES sustainment as measured by BSPI scores (arm 1 vs. arm 2). The hypothesis states that intervening with HELM will induce better sustainment (i.e., higher RUBIES fidelity) in Year 2 at Week 52 and Week 76 compared to educator coaching only. The two observations of sustainment for each educator (paired 1:1 with a child) in Year 2 are nested within the educator, who is nested within a school. For this outcome, we will fit an LMM with the following hierarchical structure: the Level 1 model (observation) will include Week 52 and Week 76 fidelity observations for each educator. This level does not include a growth model because we do not assume fidelity will systematically increase or decrease during the sustainment school year; instead, we assume random fluctuation around an educator mean for the year. At Level 2 (educator), we will include a random intercept and educator-level covariates such as years of experience which may be a potential confounder. Covariates will be selected as described above. At Level 3 (school), we will include a random intercept and a treatment assignment indicator (RUBIES + HELM vs. RUBIES only) which will be contrast coded to facilitate main effect interpretations. The coefficient for the treatment assignment indicator in this model will test whether RUBIES sustainment (i.e., level of RUBIES fidelity in the second year of study enrollment) was superior for educators assigned to RUBIES + HELM compared to educators assigned to RUBIES only at Week 52 and Week 76. As a secondary implementation outcome, we will analyze a binary indicator of RUBIES sustainment at Week 52 and Week 76 (based on the CGI-S) to evaluate whether HELM improved the odds of sustaining RUBIES at a provisional ‘sustainment’ cutoff. This analysis will use a similar model as Aim 2, but data from different timepoints or distributions (LMM and Generalized LMM for binary outcomes).

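### Both primary models choose covariates by observed between-arm imbalance (effect size of at least 0.2), so chance decides the adjustment set and the stratification factors and cohort are in neither model as written

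*Protocol article*

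**What the plan says.** The Aim 1 analyses section of the protocol article states the rule: "We will select covariates by testing for differences across arms on youth and educator characteristics", and then "covariates will be included if the effect size ≥|0.2" in absolute value. The selected covariates enter at Level 2, where they model each growth parameter of the piecewise curve. At Level 3 the section says "we will include a random intercept to account for the nesting of the child-educator dyads within schools and a treatment assignment indicator", and lists nothing else.

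The Aim 2 analyses section allows for "educator-level covariates such as years of experience which may be a potential confounder" and continues: "Covariates will be selected as described above". Its Level 3 terms are again a random intercept and the treatment indicator.

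The Randomization section has schools randomised within each cohort and adds: "Randomization will be stratified based on median split for: 1) size of school at the time of enrollment; and 2) number of possible dyads".

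The Implementation outcomes section describes a rating at implementation baseline in which the independent evaluator will "characterize the educator’s overall skill mastery at baseline on a 7-point scale". The primary Aim 2 outcome, the BSPI, is first rated at Week 16, so it has no baseline value of its own.

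**The concern.** Allocation is random, so a difference between arms on a pre-intervention characteristic is mostly chance. Its size says nothing about whether the characteristic predicts the outcome. Adjustment gains precision only from variables that do predict it. A rule keyed to imbalance can therefore admit irrelevant variables and drop strong predictors that happen to balance.

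Two further gaps leave the models open. The article gives no list of candidate characteristics. It also does not say whether a difference across arms means the primary contrast (arms 1 and 2 against arm 3) or any pair of the three arms. Two analysts could follow the text faithfully and fit different primary models.

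The screen covers youth and educator characteristics only. School size, number of possible dyads and cohort are school-level design variables, so the rule cannot bring them in, and the Level 3 terms do not list them. Where they predict the outcome, leaving them out gives standard errors that are too wide for the randomisation actually used. With 42 schools in Aim 1 and 28 in Aim 2, precision is scarce.

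**Working it through.** **Inputs** (Sample size and power section): 84 vs 42 children for Aim 1; 42 vs 42 educators in 28 schools for Aim 2; 3 dyads per school; 10% clustering; attrition of 20% (Aim 1) and 25% (Aim 2). With an intraclass correlation of 0.10 and 3 per school the design effect (DE) is 1 + 2 × 0.10 = 1.2. Read as a flat 10% inflation it is 1.1. With no clustering of the covariate it is 1.0.

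**Step 1. Reproduce the plan's own power**, to confirm that these sizes and clustering figures are the ones behind it. Two-sided 5% is assumed, since the article does not state sidedness.

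- Aim 1: control n = 42 × 0.8 / 1.1 = 30.5, RUBIES n = 61.1. SE = 6.2 × √(1/30.5 + 1/61.1) = 1.37. Power = Φ(3.8/1.37 − 1.96) = 0.790. With DE 1.2 it is 0.754.
- Aim 2: n per arm = 42 × 0.75 / 1.2 = 26.25. SE = 0.17 × √(2/26.25) = 0.0469. Power = Φ(0.13/0.0469 − 1.96) = 0.791.

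Both can be brought within about one point of the stated 80%.

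**Step 2. Chance that one covariate crosses the threshold.** With no true difference the standardised difference d has mean 0 and SE = √(DE × (1/n₁ + 1/n₂)), so P(|d| ≥ 0.2) = 2 × [1 − Φ(0.2/SE)].

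| Contrast | DE | SE | 0.2/SE | P |
|---|---|---|---|---|
| Aim 1, 84 vs 42 | 1.0 | 0.189 | 1.058 | 0.290 |
| | 1.1 | 0.198 | 1.009 | 0.313 |
| | 1.2 | 0.207 | 0.966 | 0.334 |
| Aim 2, 42 vs 42 | 1.0 | 0.218 | 0.917 | 0.359 |
| | 1.1 | 0.229 | 0.874 | 0.382 |
| | 1.2 | 0.239 | 0.837 | 0.403 |

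A simulation with 3 dyads per school and the pooled sample SD (50,000 runs) gave 0.290 and 0.334 for Aim 1, and 0.360 and 0.409 for Aim 2, at intraclass correlations of 0 and 0.1.

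**Step 3. Effect of the undefined comparison.** If any pair of the three arms may trigger inclusion, the chance per covariate is 0.63 (DE 1.0) to 0.68 (DE 1.2). This reading matches neither primary contrast, but the wording does not rule it out.

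**Step 4. How many would enter.** The number of candidates is not stated. Assuming 10 independent candidates at DE 1.2, 10 × 0.334 = 3.3 enter Aim 1 by chance and 10 × 0.403 = 4.0 enter Aim 2. With 5 candidates the figures are 1.7 and 2.0. In Aim 1 each entrant can carry up to three coefficients: the intercept and two slopes.

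**Step 5. What a prognostic covariate could gain (illustration only).** A covariate correlated r with the outcome leaves 1 − r² of the residual variance. For assumed r = 0.3 to 0.5 this removes 9% to 25%. At r = 0.3 the Aim 1 power in Step 1 would move from 0.790 to 0.826 (DE 1.1) or from 0.754 to 0.793 (DE 1.2). The 0.3 in the article is a correlation between repeated measurements on the same person, not a covariate–outcome correlation, so it does not support this figure.

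**The case against.** The strongest reply is that the rule does no inferential damage. It has a numerical threshold and uses characteristics, not outcomes. Most of these are collected before Week 16, so the set could be locked under coded arm labels before any post-baseline outcome exists. A simulation with 3 dyads per school, intraclass correlation 0.1, 10 candidates and a school-mean analysis (20,000 runs) gave a type I error of 0.051 in both aims when the covariates were not prognostic. It gave 0.038 and 0.037 when three of them were prognostic at r = 0.3. This stands. A reader might infer that the rule raises the false-positive rate or invites choosing a favourable result; the document does not support either. What remains is conservatism, lost precision and a model not yet determined.

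A reader might also infer that the baseline outcome is missing from Aim 1. It is not: the growth model starts at baseline, so baseline SESBI-R is already the first outcome observation. Likewise, the baseline mastery rating is not excluded from Aim 2. It is an educator characteristic and so a candidate under the rule, but nothing guarantees its entry.

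Finally, the article is condensed, and an analysis plan not shown could add the stratification factors. That limits the point about design factors to the models as written. It does not reach the selection rule, which the article states outright for both aims.

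**Conclusion.** The point holds. Both primary models take covariates by observed imbalance, and a characteristic with no true difference qualifies about 29–33% of the time in Aim 1 and 36–40% in Aim 2. These rates rest on the planned group sizes and design effects of 1.0–1.2. Prognostic baselines are not guaranteed entry, the candidate list and the comparison are undefined, and the school-level stratification factors and cohort are in neither model as written.

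The harm is lost precision and a primary model not fixed in advance. Its size cannot be given from the article, because covariate–outcome correlations are not reported; the 9–25% variance reduction and the count of 10 candidates are assumptions. It should be corrected, and the time is good: the Discussion reports no enrolment as of February 2026.

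**What to change.** Replace the 0.2 rule in the Aim 1 and Aim 2 analyses sections with a covariate set fixed before data are seen.

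- **Aim 1:** school-size stratum, number-of-dyads stratum and cohort, plus any prognostic baseline characteristics, each named. State which growth parameters they enter. Keep baseline SESBI-R as the first repeated outcome and do not also add it as a predictor.
- **Aim 2:** the same design factors, years of experience, and the implementation-baseline mastery rating, provided it is made before HELM begins and preferably before randomisation. The article places randomisation and implementation baseline in the same spring without giving their order, and collects that baseline in arms 1 and 2 only, so the timing needs confirming.
- **Sensitivity:** keep imbalance-based adjustment, if wanted, as a labelled sensitivity analysis with a listed candidate set and a defined contrast.

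The change is wording only; the variables named here are already collected or used in the randomisation. The downside is a few degrees of freedom: one for each two-level stratum and two for three cohorts. That is four in Aim 2 against 28 schools, and four for each growth parameter that carries them in Aim 1 against 42 schools.

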### Sample size and power

The primary focus of Aim 1 is to test the main effect of RUBIES (RUBIES + HELM and RUBIES only) vs. educator psychoeducation on change in children’s externalizing behavior from Baseline to Week 24. Assuming a Type-I error rate of 5% and SD of 6.2, a conservative within-person correlation in externalizing behavior of r = 0.3, 10% intraclass correlation (clustering within schools) for variance inflation and 20% attrition rate in children, a total of 126 autistic children paired 1:1 with educators (84 autistic children for RUBIES + HELM and RUBIES only vs. 42 children in educator psychoeducation) nested within 42 schools are needed to detect a difference of at least 3.8 points in the comparison of slopes in ABC-I with 80% power. A difference of 3.8 corresponds to a moderate standardized effect size of d = 0.62 in between groups change in children’s externalizing behavior and this effect size is clinically meaningful based on prior research [16]. The study assumed a modest clustering within schools of 10% because of the 1:1 pairing of the educator and autistic child. We expect 3 child-educator dyads per school to consent and enroll in the study. Hence, a total of 126/3 = 42 schools are needed.

For Aim 2, we will use only educators in the RUBIES + HELM vs. RUBIES only (84 educators within 28 schools) arms. With 84 educators as the effective sample size (42 each), nested within 28 schools, we have 80% power to detect a difference of at least 0.13 (or d = 0.76) in RUBIES sustainment (Week 52 and Week 76) between RUBIES + HELM vs. RUBIES only assuming SD = 0.17 based on pilot RUBIES data, a Type-I error rate of 0.05, 10% variance inflation for clustering within school effect, 25% attrition rate and within-person correlation of observations = 0.3. We assumed a higher attrition rate for educators since the turnover rate for educators are higher post pandemic.

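### As worded, the Aim 1 model allows for school clustering only through a school random intercept, which cancels from the within-child change being tested

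*Protocol article*

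**What the plan says.** - **Unit of randomisation** (Randomization): "Schools in each cohort will be randomized (1:1:1) to one of three parallel arms", with 14 schools per arm. Aim 1 therefore compares 28 RUBIES schools with 14 control schools.
- **Estimand** (Aim 1 analyses): "The primary outcome for this comparison is change in child externalizing behavior from baseline to Week 24".
- **Model** (Aim 1 analyses): a three-level linear mixed model with piecewise time and a knot at Week 16. At the child/educator level, "each growth parameter will be modeled as a function of an intercept and child/educator-level covariates". At the school level, "At Level 3 (school), we will include a random intercept to account for the nesting of the child-educator dyads within schools"; the same sentence adds the treatment indicator.
- **Test** (Aim 1 analyses): "We will test the interaction effect of treatment condition with time", followed by linear combinations of the growth parameters that give the baseline to Week 24 change. No school random effect on either time slope is named.
- **Design assumption** (Sample size and power): the variance of a between-group comparison of slopes is inflated for clustering. "The study assumed a modest clustering within schools of 10% because of the 1:1 pairing of the educator and autistic child".

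**The concern.** When schools are randomised, the variance of the treatment effect must include how much schools differ in the quantity compared. Here that quantity is change within a child. A time-constant school effect describes schools that sit higher or lower at every visit. It says nothing about schools whose children improve more or less than those elsewhere. Dyads in one school share a principal and the events of the school year and, in arm 1, the HELM programme, so school-level differences in change are plausible.

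If such differences exist and the model has no term for them, the standard error of the primary clinical effect is too small, its confidence interval too narrow and its type I error above 5%. The exploratory RUBIES mediation analyses in Aim 3 are to be built on the same model and would inherit the problem.

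**Working it through.** **1. Why the intercept cancels.** Write the score of child i in school j at visit t as y(ijt) = fixed part + u(j) + c(ij) + e(ijt), with u(j) the school intercept and c(ij) a child effect. Then y(ij,24) − y(ij,0) = fixed change + e(ij,24) − e(ij,0). Both u(j) and c(ij) are gone. Under this model, changes of two children in one school are uncorrelated.

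**2. Inputs from the protocol.** 42 schools (28 vs 14); 3 dyads per school; 84 vs 42 children; school ICC 0.10; attrition 20%, so 3 × 0.8 = 2.4 dyads per school at Week 24; difference 3.8; "Assuming a Type-I error rate of 5% and SD of 6.2"; "a conservative within-person correlation in externalizing behavior of r = 0.3". Two-sided testing is my assumption, as sidedness is not stated.

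**3. The plan's own figure.** Effective group sizes are 84 × 0.8/D and 42 × 0.8/D, with D the design effect, and power = Φ(3.8/SE − 1.96).
- SD 6.2, D = 1.10: 61.1 vs 30.5, SE 1.374, power 0.790.
- Baseline-adjusted SD 6.2 × √(1 − 0.3²) = 5.91, D = 1 + 2 × 0.10 = 1.20: 56 vs 28, SE 1.369, power 0.793.
- The same SD, D = 1 + 1.4 × 0.10 = 1.14: SE 1.334, power 0.813.

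The stated 80% is reproduced, but by more than one route. The figure therefore confirms that a clustering allowance was made, not which ICC it refers to.

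**4. Actual type I error when changes are correlated within schools.** Let ρ be the school ICC of change, which the protocol does not give. The true variance of the contrast is the model variance times D = 1 + (m − 1)ρ, where m is dyads per school. Actual error = 2 × [1 − Φ(1.96/√D)]. At ρ = 0.10 and m = 3: √1.20 = 1.095, 1.96/1.095 = 1.789, error 7.4%, and the SE is 1 − 1/1.095 = 8.7% too small.

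| ρ | m = 3: D | error | SE too small by | m = 2.4: D | error | SE too small by |
|---|---|---|---|---|---|---|
| 0 | 1.00 | 5.0% | 0% | 1.00 | 5.0% | 0% |
| 0.05 | 1.10 | 6.2% | 4.7% | 1.07 | 5.8% | 3.3% |
| 0.10 | 1.20 | 7.4% | 8.7% | 1.14 | 6.6% | 6.3% |
| 0.20 | 1.40 | 9.8% | 15.5% | 1.28 | 8.3% | 11.6% |

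**5. Check by simulation.** 42 schools × 3 dyads × 3 visits, complete data, no treatment effect, 10,000 runs per value. Rejection rates at ρ = 0, 0.05, 0.10 and 0.20:
- random-intercept analysis: 5.1%, 6.0%, 7.6%, 9.8%;
- with child-level random change added: 5.0%, 6.1%, 7.5%, 9.7%, so a child slope does not repair it;
- t-test on school means (40 df): 5.2%, 4.9%, 5.1%, 5.5%.

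**6. Check with dropout.** With missing visits the cancellation is close but not exact. A generalised least squares calculation compared the model-based with the true variance when 20% are lost by Week 24, half before and half after Week 16. The error is 6.0%, 7.0% and 9.1% at ρ = 0.05, 0.10 and 0.20. The 2.4-per-school formula is the cruder, lower figure.

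**7. How often the added variance would be estimated as zero.** With balanced data, the ratio of between-school to within-school mean squares has expectation ratio (1 + 2ρ)/(1 − ρ) on 40 and 84 df. A moment estimate is zero or negative when F(40,84) falls below the inverse of that ratio. At ρ = 0.10 this is F < 0.9/1.2 = 0.75, probability 16%. At ρ = 0.05 it is F < 0.95/1.10 = 0.864, probability 31%.

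**The case against.** **The wording may mean more than one intercept.** In multilevel notation the treatment indicator must enter the school-level equations for the slopes, or there would be no treatment-by-time effect. The random term in the same sentence might enter them too, which would give school random slopes. This is possible, but the wording is singular, and the Aim 2 section uses the same phrase for a model without growth terms, where it can only mean a plain school intercept. What stands is that the article condenses the model. The intended model may be sound, and the text should say so.

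**The harm is conditional.** A reader might infer that the primary p-values are bound to be too small, or that the analysis flatly contradicts the power calculation. The protocol does not support either. If schools do not differ in change, the error rate is 5.0%. The 10% ICC is not identified as one of scores or of change; if it describes stable differences in scores, a school intercept represents it properly. Its use in a comparison of slopes suggests change but does not settle it.

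**This belongs in the analysis plan.** That is true of the within-child covariance structure, and its absence is no fault. It is not true of the school term, which the article names along with its purpose.

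**The repair is not free.** With about three dyads per school, the school variance in change will be poorly estimated and sometimes estimated as zero. This stands, and it is why a fallback is needed.

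**Conclusion.** The point holds in conditional form. Read plainly, the stated school term does not do what it is said to do for the contrast being tested, and any resulting error is anti-conservative. Assuming two-sided testing and an ICC of change of 0.10, type I error is about 6.6% to 7.4%. The lower figure takes 2.4 dyads per school, the upper figure complete data, and the explicit dropout calculation (7.0%) lies between them. Nominal 95% intervals would then cover about 93%. The 8% to 10% range needs twice the protocol's ICC. The inflation is moderate because clusters are small. It is still worth removing, since it affects the primary clinical test and no participants had been enrolled as of February 2026.

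**What to change.** In the Aim 1 analyses, state that the school-level random effects apply to the growth terms, either as a school-by-time effect or as a school random effect on the baseline to Week 24 change. Base inference on the 42 schools. Prespecify what replaces this if the school variance in change is estimated as zero: a school-level summary analysis, or cluster-robust inference with a small-sample correction. In the sample size section, say whether the 10% ICC refers to scores or to change. The within-child covariance structure can be left to the SAP.

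This is a wording change with no effect on data collection. The price is a wider interval: at an ICC of change of 0.10, by a factor of √1.14 = 1.07 to √1.20 = 1.10. The sample size already includes an allowance for clustering, and the first route in the working, with a 1.10 inflation, gives 79% power. If the full design effect of 1.20 is applied to an SD of 6.2, power is 75%; with the baseline-adjusted SD it is 79%.
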